**Figure 4 figure4:**
[figure not shown]
Analytical details of the tongue diagnosis.

**Figure 5 figure5:**
[figure not shown]
Tongue analysis examples of body constitutions and syndrome differentiation.

#### Syndrome Differentiation

The syndrome differentiation of *xiao-ke* will be based on the objective assessment results analyzed from CCMQ, tongue, and pulse diagnosis regardless of the participants’ group status. Data collection under standardized conditions using contemporary diagnostic devices is expected to enhance stability and reliability in syndrome differentiation. This approach effectively minimizes bias and eliminates the necessity for blinding in our study design.

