### Recruitment of Participants

To ensure a sufficient sample size for statistical analysis of the diabetic and prediabetic syndrome differentiation, we intend to recruit 250 participants who will be equally assigned to one of 5 arms. The groups are as follows: group 0: healthy or subhealthy without diabetes, hypertension, or dyslipidemia; group 1: prediabetes without hypertension or dyslipidemia; group 2: diabetes without hypertension or dyslipidemia; group 3: prediabetes with hypertension and dyslipidemia; and group 4: diabetes with hypertension and dyslipidemia. Primarily, recruitment is conducted through physician referrals, as well as recruitment posters on the institution’s bulletin boards and social media. Participants can register through the digital registration form, while the screening and enrollment will be conducted by the study team. The list of potential participants will be consolidated, and the research assistant will contact the participants to guide them through the informed consent process. Written consent will be collected when informed consent has been explained to the participant in a language they can comprehend. The participants will have the opportunity to decline enrollment at any time, and they are not required to present a justification for doing so. A study ID based on the grouping will be assigned after screening and enrollment according to the inclusion and exclusion criteria. The first 50 participants who qualify for each of the 5 groups and complete the screening process will be included, and recruitment for that particular group will cease once the target number is reached. This ensures that each of the 5 groups has an equal number of participants, allowing for balanced and effective statistical analysis.

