### Study Procedure and Outcome Measures

Table 3 shows the study schedule for enrollment and assessment, which may take between 0.5 hours and 1 hour in a single visit. The assessment and evaluations will take place in a temperature-controlled environment of 25 °C. The study team has undergone training by the principal investigator on the use of questionnaires, pulse sphygmograph, and tongue diagnostic devices to reduce interphysician variability.

**Table 3 table3:** The study schedule.

		Enrollment	Allocation	Postallocation	
Timepoint		–*t*_1_	0	*t* _1_	*t* _2_

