#### Pulse Sphygmograph

The Asia Plus Pen Pulse Analysis System Model PPAS-93 (Asia Plus Biotech Co, Ltd) will be used to identify pulse profiles.

The PPAS-93 is a noninvasive device that comprises a high-precision pressure sensor pen and a pulse analyzer. The high-precision pressure sensor pen is a portable handheld pen that digitalizes the biological signal of the radial pressure pulse wave and provides graphical analysis using fast Fourier transformation. This electronic gadget incorporates a high-precision pressure sensor, a filter, an amplifier, and a signal recording card connected to signal analysis software. The sampling rate is 3000 Hz, and the frequency response is between 0.1 and 50 Hz.

With the participant sitting in a relaxed position, the *cun, guan,* and *chi* pulses of each hand will be assessed using the sensor pen with appropriate vertical pressure. The result will be recorded when the best spectrogram displays the highest amplitude. A summation of SE in the 0-10 Hz (SE_0-10Hz_), 10-50 Hz (SE_10-50Hz_), and 13-50 Hz (SE_13-50Hz_) frequency ranges will be obtained. Figure 1 depicts the pulse sphygmograph and its application output.

The time domain analysis examines the amplitude and shape of the arterial waveform such as surging, slippery, fine, and thready [30]. The pulse rate per minute can be determined by the number of waves in 6 seconds multiplied by 10. This will determine the rate such as a rapid or slow pulse. The frequency domain analyzes the variation of SE in the radial pulse waves [30]. The quantitative measures can assess the intensity and density of the SE, providing insight into the deficiency, repletion, coldness, heat, or dampness syndrome. An in-depth examination of both the time and frequency domains will be conducted to deduce the associated syndrome-etiology differentiation of *xiao-ke* (Table 2).

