#### Tongue Diagnosis

The China Artificial Intelligence Health Status Identification System Model YZKJ-SMZY-1AI will be used to image and analyze the participant’s tongue. The noninvasive device captures the image of the tongue through an inbuilt camera supported by light-emitting diode lighting within the device within 15 seconds. A monitor connected to the imaging instrument would display real-time video feedback on the tongue’s position. Using an artificial intelligence system, the photographs of the face, tongue, and sublingual collaterals will be examined and compared with typical images of tongue analysis within 10 seconds. Figure 4 depicts the analytical details of the tongue, including the shape and color of the tongue, the texture and color of the tongue coating, the moisture level of the tongue, and the sublingual collaterals. The body constitution and syndrome differentiation will be analyzed and recorded. Figure 5 provides some examples of body constitutions and syndrome differentiation reported from the system. The results will be reconciled with the pulse diagnosis and CCMQ.

Before evaluation, the participants will be instructed to abstain from tongue scraping, smoking, and consuming caffeinated beverages such as coffee, tea, and cola, as well as dairy products such as milk, yogurt, and cheese, which may alter the tongue diagnosis.

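### Device-based collection does not make blinding unnecessary: the study ID is built on group, and pulse capture and syndrome assignment still rest on judgement

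*Protocol article*

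**What the plan says.** In Methods, Syndrome Differentiation, the syndrome is to rest on "objective assessment results analyzed from CCMQ, tongue, and pulse diagnosis regardless of the participants’ group status". Because the devices are used under standardised conditions, the section concludes: "This approach effectively minimizes bias and eliminates the necessity for blinding in our study design". The abstract and the Discussion (Expected Findings) likewise expect unbiased results.

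Other parts of Methods describe how the data arise:

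- Recruitment of Participants: "A study ID based on the grouping will be assigned after screening and enrollment according to the inclusion and exclusion criteria". In the same section, "the screening and enrollment will be conducted by the study team".
- Study Procedure and Outcome Measures: "The study team has undergone training by the principal investigator on the use of questionnaires, pulse sphygmograph, and tongue diagnostic devices". Table 3 places allocation at time 0, the health evaluation (including blood sugar, medications and symptoms) at t1, and pulse and tongue assessment at t2.
- Pulse Sphygmograph: the sensor is a handheld pen, and the pressure is described as suitable without a numeric target. "The result will be recorded when the best spectrogram displays the highest amplitude". Time- and frequency-domain findings are then used to deduce the syndrome.
- Tongue Diagnosis: an AI system analyses the images, and then "The results will be reconciled with the pulse diagnosis and CCMQ". No rule for reconciling is given.

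**The concern.** Blinding can be dispensed with only if nobody who could influence the recorded value or its interpretation has room to do so, or if nobody with that room knows the group. The protocol secures neither condition, yet it states that blinding is not needed.

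Two results are at stake. SE13-50Hz is the one pulse variable named in the hypothesis and in the ANOVA, and syndrome differentiation is the subject of the study. If knowledge of group affects how the pulse is taken or how conflicting sources are reconciled, the error follows the very factor being compared. The ANCOVA adjusts for sex, age, BMI, physical activity and similar variables, none of which captures an assessor's expectations. Recruiting more people makes such an error more precisely estimated, not smaller.

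**Working it through.** The sentence rests on no figure, so the check is a comparison of passages, followed by an illustration of scale.

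**1. Can group be known at measurement?** The ID is based on group and assigned once eligibility is settled, before t1 and t2 in Table 3. The study team screens and enrols, and the study team is trained on the questionnaires and both devices. No masked operator, separate reader or concealed code is mentioned. Elsewhere the identifier is called unique or distinct, but that serves confidentiality and does not hide group.

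**2. Is there room for judgement?**

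- Pulse capture: yes. Pressure is left to the person holding the pen, and so is the decision that the best spectrogram has been reached. Highest amplitude is a criterion, but no limit on searching or number of attempts is given.
- Syndrome from pulse plots: yes, as described, since it is deduced from an examination of both domains.
- Reconciliation of tongue, pulse and CCMQ: yes, since no rule is stated.
- CCMQ: this is a Likert-scale questionnaire answered by participants, yet Syndrome Differentiation counts it among the objective results.
- Tongue imaging: little. Lighting is built in and an AI system does the comparison.

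**3. Is there a safeguard?** The only one is that syndromes are assigned regardless of group. That states an intention and conceals nothing.

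**4. Illustration of scale.** Inputs from the protocol: 50 per group, two-tailed tests, alpha 0.05, Bonferroni correction. The bias b, in SD units, is assumed; the protocol gives no SD or effect size for SE13-50Hz in this study.

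- Standard error of a standardised difference: sqrt(2/50) = 0.20.
- False-positive probability when there is no true difference: Φ(b/0.20 − z) + Φ(−b/0.20 − z).
- At alpha 0.05 (z = 1.960), b = 0.1, 0.2 and 0.3 give 7.9%, 17.0% and 32.3%.
- At alpha 0.05/4 = 0.0125 (four comparisons with control), the same biases give 2.4%, 6.7% and 15.9%.
- With an assumed 100 per group the standard error is sqrt(2/100) = 0.141. For b = 0.2 at alpha 0.05, Φ(1.414 − 1.960) + Φ(−1.414 − 1.960) = 0.293, or 29.3% instead of 17.0%. A larger sample makes a fixed bias more likely to be declared significant.

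**The case against.** The best defence is that the protocol does a good deal to standardise measurement. It specifies a temperature-controlled room, operator training, a numerical pulse output and AI analysis. The Conclusions say that both devices derive constitution and syndrome by algorithm. The study is also exploratory, has no intervention, and calls itself a pilot. This stands for tongue imaging, where the concern is weak. It does not cover the handling of the pen or the reconciliation step, and training reduces variation between operators without hiding group from them.

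A reader might infer more than the documents support:

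- **That every step is done with group known.** The text permits this but does not state it. The ID format is not given, the pulse and tongue sections name no operator or reader, and Table 3 does not say that one person does both t1 and t2.
- **That several traces are taken and the largest kept.** The pulse section can equally mean adjusting the pen until the signal peaks and recording once. Any inflation computed from a best-of-several rule would need an assumed difference in attempts between groups, and full correlation between amplitude and SE13-50Hz. The protocol supports neither.
- **That bias would favour a hypothesised direction.** None is stated: SE13-50Hz may reflect a difference, and tests are two-tailed.

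**Conclusion.** The statement that blinding is unnecessary is wrong as written. A group-based ID, a screening team also trained on the devices, operator-dependent pulse capture and an unspecified reconciliation together leave SE13-50Hz and the syndrome call open to bias from knowledge of group. The conclusion is firm for the sentence and the ID scheme, strongest for pulse and reconciliation, and weak for tongue imaging.

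The size of any bias cannot be derived from the documents. The false-positive rates above depend wholly on an assumed bias and show only that modest distortions would matter at 50 per group. Nothing in the protocol shows that bias has occurred.

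**What to change.** - Delete or soften the sentence in Syndrome Differentiation, and temper the claims of unbiased results in the abstract and Discussion. Describe the CCMQ as a questionnaire.
- Use sequential study IDs that carry no group code.
- Re-code the stored pulse and tongue PDFs for all participants, including those already enrolled, and assign and reconcile syndromes from them without access to group.
- For the remaining participants, where existing staffing allows, have pulse and tongue taken by a trained team member who did not do that person's screening or health evaluation.
- Record the operator and use it in a sensitivity analysis.

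The cost is some re-coding work and a change in work order. There is a limit to state openly: 140 of 250 (56%) were enrolled by 15 July 2024. For them, reading can be masked but pulse capture cannot be redone.

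Two further changes are not advised. Switching mid-study to the mean of several traces would create two measurement eras, and because each group closes separately at 50, era could be confounded with group. Adjusting for palpating pressure could remove real differences between groups.

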### Ethical Considerations

The final clinical trial protocol version 1.8 dated August 1, 2023, was reviewed and approved by the Parkway Independent Ethics Committee (PIEC/2022/003). Important protocol modifications will be communicated to all study staff via emails and meetings after PIEC approval. Informed consent will be obtained from all participants by investigators who are approved by the ethics committee. The participants will be given the right to reject participation at any time. The collected data will be deidentified. Reimbursement in the form of cash vouchers will be provided to the participants upon completion of the study.

### Data Management and Monitoring

Without interference from the study sponsor, the data will be monitored by the principal investigator and the study team. Each participant will be assigned a distinct identifier upon enrollment to guarantee the confidentiality of their information.

The reports generated by the tongue diagnosis imaging device and pulse sphygmograph will be stored as PDFs. Each participant’s information will be documented in an encrypted Microsoft Excel spreadsheet for comparison purposes. No data will be omitted over the duration of the trial. Outliers and missing data will be identified to ensure data quality. All the assessment and evaluation results will be digitized and archived in Microsoft SharePoint with a password-protected database available exclusively to the research staff for at least 6 years following the conclusion of the study before being discarded by the principal investigator.

We anticipated that the study would be completed within the allotted time frame and that there would be no significant participant safety concerns. Consequently, a data monitoring committee and stopping guidelines are unnecessary. Interim analysis may be conducted without stopping the study.

There are no possible risks and side effects from this study as the diagnostic assessments are noninvasive. Hence, adverse events associated with the study are not anticipated.

### Statistical Analyses

The baseline variables (age, sex, height, body weight, BMI, and blood sugar levels), MET-minutes for physical activity, scoring of body constitution, pulse assessments, and tongue analysis results will be compared between the five groups.

Using ANOVA, we will compare the variances across the means of the SE_13-50 Hz_ value from the pulse sphygmograph between each group and the control. Analysis of covariance will also be used to assess the group differences while controlling for potential confounding variables such as gender, age, BMI, physical activity levels, and others. Using the Bonferroni test for post hoc multiple comparisons, the mean values will be compared and corrected. Chi-square tests will also be used to do the comparative analysis of the body constitutions or syndromes between the objective and subjective assessments. All tests will be 2-tailed and *P*<.05 will be considered statistically significant. We will use STATA (standard edition version 18.0; StataCorp LLC) for the analysis.

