### Specific Aims and Hypothesis

This study aims to identify the gap in syndrome differentiation between the subjective and objective TCM diagnosis. We devised a protocol for a nonrandomized, exploratory, observational case-control study with equal allocations in 5 arms to investigate the syndrome differentiation of diabetes and prediabetes. We hypothesize that the local TCM syndrome differentiation of diabetes and prediabetes in the tropical climate may differ from that defined based on the Chinese demographic. We also speculate that the high-frequency spectral energy (SE_13-50Hz_) may reflect a difference in pulse wave intensity and density between the healthy and diabetes groups. We will validate the syndrome differentiation using contemporary technologies such as the tongue imaging device and the pulse sphygmograph. An objective diagnosis of the tongue could be achieved with the advancement of artificial intelligence and imaging technology [36,37]. Images of the tongue captured with the tongue diagnostic device will then be processed through an algorithm for comparison and analysis against standard tongue diagnosis images (Figure 2). Furthermore, the development of pulse sphygmographs has enabled the digitalization of pulse assessment. Researchers investigated quantitative analyses of pulse profiles in the time and frequency domains [30]. The development of these quantitative and graphical representations of the pulse profiles in the 6-pulse positions is a significant step toward transforming traditional pulse diagnoses into scientific and objective assessments (Figure 1) [31].

The objective assessment will potentially increase the accuracy of the identification, diagnosis, and prevention of diabetes and prediabetes through a targeted treatment system tailored to the local population.

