## Discussion

### Expected Findings

We anticipate that diabetes and prediabetes with or without hypertension and dyslipidemia would have different body constitutions compared to healthy individuals. The prevalence of specific TCM syndrome differentiation may be more common in countries with hot and humid tropical climates, albeit it may differ from the Chinese demographic.

TCM diagnosis is a comprehensive approach that integrates observation, inquiry, pulse palpation, and tongue diagnosis. Finger sensitivity required for palpating radial pulses and precise visual assessment of the tongue are fundamental to accurately detecting variations in the pulse and tongue quality in TCM diagnosis. However, traditional methods of syndrome differentiation are highly subjective and skill dependent. The interpretation of pulse quality and tongue characteristics can differ across practitioners based on their clinical training, experience, and personal bias. This may result in observations lacking clinical significance. To mitigate subjectivity and provide impartial evaluations, we designed this protocol to examine the syndrome differentiation of patients with diabetes and those with prediabetes using contemporary TCM diagnostic technologies. The data collected and evaluated under standardized conditions using these contemporary diagnostic devices are expected to yield stable and unbiased results. This standardized assessment will facilitate more consistent and reliable syndrome differentiation, which is crucial for both clinical practice and research. Thus, our findings may enhance the accuracy of the identification, diagnosis, treatment, and prevention of diabetes and prediabetes through targeted approaches, potentially improving patient outcomes and management effectiveness. Additionally, we will explore and analyze the correlation between TCM syndrome differentiation and WHO diagnosis criteria for diabetes. Establishing the reliability of contemporary TCM diagnostic tools sets the stage for their broader adoption in clinical practice and enables future research into individualized treatment plans based on objective TCM syndrome differentiation. Some of the following study challenges are expected.

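### Post hoc Bonferroni is valid for the four group-versus-control contrasts of SE13-50Hz, but Dunnett or Holm would protect the same familywise error with slightly more power

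*Protocol article*

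**What the plan says.** The Statistical Analyses section sets up an ANOVA of the SE13-50Hz "value from the pulse sphygmograph between each group and the control", followed by an analysis of covariance for group differences. The correction of the group means comes next: "Using the Bonferroni test for post hoc multiple comparisons". The general rule is "All tests will be 2-tailed and *P*<.05 will be considered statistically significant".

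Other sections put the question the same way. Under Specific Aims and Hypothesis, SE13-50Hz "may reflect a difference in pulse wave intensity and density between the healthy and diabetes groups". Under Expected Findings, the disease groups "would have different body constitutions compared to healthy individuals". The one broader statement opens the Statistical Analyses section: baseline variables, activity, constitution scores, pulse assessments and "tongue analysis results will be compared between the five groups". No pair of disease groups is named as a question for SE13-50Hz, and the number of comparisons in the Bonferroni family is not given.

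**The concern.** Four contrasts against one control are a standard many-to-one problem. Bonferroni takes no account of the correlation that the shared control creates, and it does not step down once a contrast has been rejected. Dunnett uses the correlation and Holm steps down. Both hold the familywise error at 5% for the same four contrasts, and neither is less powerful than Bonferroni.

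What is at stake is power. Recruitment stops at 50 in each group (Recruitment of Participants). The Sample Size Calculation section gives no difference, SD or numeric power for this study, so the choice of correction is one of the few ways left to affect what the study can detect.

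**Working it through.** **Inputs from the article.** Five equal groups of 50, 250 in total; error df = 250 − 5 = 245; two-sided alpha 0.05; four contrasts against control. The number of possible pairs is 5 × 4 / 2 = 10, of which 10 − 4 = 6 are between disease groups.

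**Assumption.** The article gives no mean or SD for SE13-50Hz, so differences are in SD units (d), taken over 0.4 to 0.8. For the same reason the planned 50 per group cannot be reproduced from a power formula. Inverting the usual two-group formula without multiplicity, d = (1.960 + 0.842) × √(2/50) = 0.56 at 80% power.

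**Critical values for |t| on 245 df.**
- Bonferroni over 4: the t quantile at 1 − 0.05/8, which is 2.52 (per-contrast alpha 0.0125).
- Bonferroni over 10: the t quantile at 1 − 0.05/20, which is 2.83 (per-contrast alpha 0.005).
- Dunnett over 4: the 95th percentile of the largest |t| among four contrasts with correlation 0.5, by simulation, which is 2.46 (per-contrast alpha 0.0146).

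**Power per contrast.** Noncentral t with noncentrality d × √(50/2) = 5d.

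| d | Bonferroni, 4 | Dunnett, 4 | Bonferroni, 10 |
|---|---|---|---|
| 0.4 | 30.5% | 32.5% | 20.5% |
| 0.5 | 49.5% | 51.7% | 37.2% |
| 0.6 | 68.6% | 70.5% | 56.7% |
| 0.66 | 78% | 80% | 68% |
| 0.7 | 83.6% | 85.0% | 74.7% |
| 0.8 | 93.0% | 93.7% | 87.7% |

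The difference detectable with 80% power is 0.67 SD (Bonferroni over 4), 0.66 SD (Dunnett) and 0.74 SD (Bonferroni over 10). In sample-size terms at d = 0.6, 80% power needs 63, 61 and 75 per group.

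**Holm on the four contrasts** (200,000 simulated trials, d = 0.6). If all four effects are real, power per contrast is 77.4% against 68.6% for Bonferroni over 4, a gain of about 9 points. If only one is real, it is 68.6% for both, a gain of 0.

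**Familywise error over the four contrasts when no group differs.** Dunnett 5.0%, Holm 4.3%, Bonferroni over 4 4.3%, Bonferroni over 10 1.8%. None exceeds 5%.

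**The case against.** The strongest reply is that nothing here is wrong. Bonferroni is valid and conventional, and the study is exploratory and calls itself a pilot. On the four-contrast reading, which the article's own wording favours, Dunnett saves only two participants per group at d = 0.6. One simple correction that serves both the ANOVA and the ANCOVA is defensible. All of this stands, and it limits the point to a small improvement.

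A reader might infer that the plan corrects for all 10 pairs and so gives up 12 points of power. The text does not say that. A post hoc test after a five-group ANOVA is often run that way, but the family is left open, and a condensed article may leave that detail to the full protocol or analysis plan.

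A reader might also infer that the change is free. On the four contrasts it is: Holm needs no added assumption, and Dunnett uses the normal, equal-variance model of the ANOVA. It is not free if the six disease-group pairs were meant to be protected. The groups separate prediabetes from diabetes, each with and without hypertension and dyslipidemia, so such comparisons are a plausible purpose. Part of the 12 points would then be bought by dropping error control on those pairs.

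The reply does not remove the core. For the question as the article states it, methods with the same error control and at least the same power are available.

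**Conclusion.** The point holds as a minor efficiency gain. For the four stated contrasts, Bonferroni is valid but is outperformed or matched by Dunnett and Holm at the same 5% familywise error. The secure gain is about 1 to 2 points per contrast with Dunnett over d = 0.4 to 0.8, or 0 to about 9 points with Holm at d = 0.6, depending on how many effects are real. The 12-point figure at 0.66 SD is conditional on an all-pairs family that the article does not state, so it should not be reported as the size of the loss. All power figures rest on assumed standardised differences, equal variances and 50 evaluable participants in each group.

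**What to change.** In the Statistical Analyses section, name the four group-versus-control contrasts of SE13-50Hz as the family for multiplicity control. Replace Bonferroni with Dunnett for the unadjusted means, or with Holm across the four ANCOVA-adjusted contrasts. State that comparisons between disease groups form a separate exploratory set, labelled as such, or Holm-corrected within that set if protection is wanted.

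The cost is a short change of wording, to be made before the data are analysed, with no extra participants or data. Two downsides should be accepted openly: the six disease-group pairs fall outside the main familywise control, and Holm does not give simple simultaneous confidence intervals.
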